**Methods/design:**

Health professionals from the disciplines of nursing, occupational therapy, speech pathology, dietetics, physiotherapy or radiation therapy will participate in training to deliver the psychosocial Intervention focusing on core concepts of supportive-expressive, cognitive and dignity-conserving care. Health professional training will consist of completion of a self-directed manual and participation in a skills development session. Participating health professionals will be supported through structured clinical supervision whilst delivering the Intervention. In the stepped wedge design each of the 5 participating clinical sites will be allocated in random order from Control condition to Training then delivery of the Intervention. A total of 600 patients will be recruited across all sites. Based on level of distress or risk factors eligible patients will receive up to 4 sessions, each of up to 30 minutes in length, delivered face-to-face or by telephone. Participants will be assessed at baseline and 10-week follow-up. Patient outcome measures include anxiety and depression, quality of life, unmet psychological and supportive care needs. Health professional measures include psychological morbidity, stress and burnout. Process evaluation will be conducted to assess perceptions of participation in the study and the factors that may promote translation of learning into practice.

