### Intervention

This study comprises two discrete components:

a) Training of health professionals who will deliver the psychosocial Intervention

b) Delivery of the psychosocial Intervention by the trained health professionals.

The design for this randomised study is a stepped-wedge cluster design, a type of crossover design in which different clusters (the clinical sites) cross over in one direction only, from Control to Training then Intervention [28]. At the conclusion of the study, all sites will have received Training and be providing the Intervention [29] delivered by health professionals who have received training at that site as depicted in Table 1.

**Table 1 T1:** Stepped wedge design.

	Epoch 1	Epoch 2	Epoch 3	Epoch 4	Epoch 5	Epoch 6	Epoch 7
Site 1	Control	TRAINING	**Intervention**	**Intervention**	**Intervention**	**Intervention**	**Intervention**

Site 2	Control	Control	TRAINING	**Intervention**	**Intervention**	**Intervention**	**Intervention**

Site 3	Control	Control	Control	TRAINING	**Intervention**	**Intervention**	**Intervention**

Site 4	Control	Control	Control	Control	TRAINING	**Intervention**	**Intervention**

Site 5	Control	Control	Control	Control	Control	TRAINING	**Intervention**

Week	1	10	20	30	40	50	60

The Intervention is sequentially rolled-out across sites in random order over a number of time periods (Epochs).

The nature of the Intervention will be *tailored to the level of need of the patient*, eligible patients receiving a "low-intensity" or "medium-intensity" Intervention, allocated according to the Algorithm depicted in Table 2.

**Table 2 T2:** Algorithm for patient allocation to Intervention

DT^1 ^score <4		DT^1 ^score 4 or greater		
No risk factors	+ risk factors^2^ HADS^3 ^< 8	+/- risk factors^2^ HADS^3 ^< 8	+/- risk factors^2^ HADS^3 ^8-21	+/- risk factors^2^ HADS^3 ^22 or greater

Usual care	**Low-intensity Intervention** Patient self-directed resource suite only		**Medium-** **intensity** **Intervention** Tailored psychosocial Intervention delivered by trained Health Professional	Specialised Treatment with an appropriately qualified practitioner via a pre-defined clinical pathway

DT^1^: Distress Thermometer

Risk Factors^2^: Risk factors as identified in the National Breast and Ovarian Cancer Centre Psychosocial Checklist (PSCL)

HADS^3^: Hospital Anxiety and Depression Scale

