#### Patients

Inclusion criteria are: (1) aged 18 years or over (2) consecutive patients attending outpatient oncology clinics at each site (3) currently receiving active treatment for cancer OR have completed active treatment within the previous 2 months OR have been diagnosed with recurrent/advanced cancer within the previous 2 months. Exclusion criteria are: (1) inability to speak and read English, (2) receiving current specialised psychological treatment from a psychologist, psychiatrist, or other trained counsellor, (3) currently taking antidepressant medication, (4) health status precludes ability to complete questionnaires and participate in up to four psychosocial Intervention sessions and follow-up at 10 weeks, and (5) recruited in any previous Epoch of this study (that is, patients can only participate during one Epoch).

We will recruit 20 patients per site per Epoch (with the exception of the Training Epochs during which no patients will be recruited) with a total sample size of 600 patients. No patient who has been recruited in a previous Epoch will be eligible to participate in subsequent Epochs. Primary outcome measure is change in HADS score over ten weeks from enrolment to follow-up. Estimates of HADS in similar populations [35] are a mean of 17.8 with SD = 9.0, with a 10%-15% difference in mean change-scores assumed to be clinically significant. To detect this difference, with power = 80%, in a before-after design assuming a correlation 0.5 within patient over time, about 200 patients in each group are needed (Stata IC, version 10). Patients will be clustered by clinic, but we have no data on which to estimate intraclass correlation for the HADS scores; so will assume a design effect of deff = 1.5 to accommodate clustering, and hence we will require 600 patients in all; across five clinics, so we will seek to enrol 120 patients per site.

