### Statistical analyes

#### Quantitative analysis

We will compute and compare the average change in HADS scores among patients enrolling during Intervention Epochs with scores of patients enrolling during Control Epochs. The strength of the stepped-wedge design is that we will be able to account for systematic differences between sites and times during the trial, and also for case-mix differences between patients.

We will use a patient-level hierarchical analysis model to accommodate these potentially confounding factors. With this model, we can adjust for case-mix differences between sites, as well as allow for specific site characteristics (other than presence/absence of the Intervention). A generalised estimating equation (GEE) linear or logistic model will be implemented [28] to estimate the effect of the Intervention on the patients' change in HADS scores and the prevalence of depression "caseness" at each site. Stata Version 10 (StataCorp, 2008) will be used for all statistical analyses.

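### The primary GEE analysis rests on 5 site clusters with no small-sample safeguard, so its usual implementations would reject a true null well above 5%

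*Protocol article*

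**What the plan says.** The Patients section makes change in HADS score over ten weeks the primary outcome. The Quantitative analysis section gives the method for that outcome and for caseness: "A generalised estimating equation (GEE) linear or logistic model will be implemented [28] to estimate the effect of the Intervention". Just before, it describes the approach as hierarchical: "We will use a patient-level hierarchical analysis model to accommodate these potentially confounding factors". It adds that "we can adjust for case-mix differences between sites, as well as allow for specific site characteristics". It also says the design allows for differences between sites and between times, but not in what form.

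The number of clusters is fixed elsewhere. The abstract states that "each of the 5 participating clinical sites will be allocated in random order", and the Intervention section confirms the unit: "different clusters (the clinical sites) cross over in one direction only, from Control to Training then Intervention". On recruitment, the Patients section says "We will recruit 20 patients per site per Epoch (with the exception of the Training Epochs during which no patients will be recruited", and the total is spread "across five clinics, so we will seek to enrol 120 patients per site".

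The same section says no data exist from which to estimate an ICC for HADS, and it allows for clustering through a design effect of 1.5. The article names no working correlation, standard-error type, reference distribution, degrees-of-freedom rule or significance level.

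**The concern.** GEE standard errors are justified as the number of independent clusters grows. Here there are 5. If time is modelled by epoch, the mean model has 8 parameters (7 for epochs, 1 for Intervention), more than there are clusters. The sandwich estimator then builds its variance from 5 cluster contributions whose residuals have been shrunk by the fit, so it is too small on average and very variable. A normal reference ignores both faults. An exchangeable model-based standard error avoids the sandwich, but it relies on a correlation estimated from 5 sites and on there being no extra variation between epochs within a site.

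The design effect of 1.5 does not help: it raises the number of patients and leaves the validity of the test as it was. At stake is the primary conclusion, since an ineffective intervention could be declared effective much more often than the nominal rate, with confidence intervals too narrow to match.

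**Working it through.** **The plan's own figure.** The article states no false-positive rate; its only related figure is the sample size. With SD 9.0 and within-patient correlation 0.5, the SD of change is 9 × √(2 × (1 − 0.5)) = 9.0. Using n per group = 2 × (1.960 + 0.842)² × 81 / δ², with percentages taken on the mean of 17.8:

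- 10% (δ = 1.78): 402
- 12.5% (δ = 2.225): 257
- 15% (δ = 2.67): 179

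The stated 200 per group matches δ = 2.52 (14.2%), and 2 × 200 × 1.5 = 600. The total is thus reproduced. A design effect of 1.5 implies an ICC of 0.5/119 = 0.0042 if the cluster is 120 patients, or 0.5/19 = 0.026 if it is the 20 in a cell.

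**Layout.** Table 1 has 5 × 7 = 35 cells. Removing 5 Training cells leaves 30 (15 Control, 15 Intervention), and 30 × 20 = 600.

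**Assumptions not in the article.** Two-sided 5% level; ICC 0 to 0.10; correlation of site effects between epochs from 1 (no site-by-epoch variation) down to 0.5.

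**Simulation under no effect.** Linear GEE clustered on site, 2,000 trials per setting (Monte Carlo error about 0.5 points at a 5% rate and 1 point at 30%). Ranges are over the ICC settings.

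| Mean model | Working correlation | Uncorrected sandwich, normal | Model-based, normal |
|---|---|---|---|
| Epoch effects | exchangeable | 27–37% | 7–16% |
| Epoch effects | independence | 25–34% | 5–38% |
| Linear time | exchangeable | 18–29% | 10–16% |
| Linear time | independence | 19–26% | 5–40% |
| No time term | exchangeable | 16–24% | 7–13% |
| No time term | independence | 15–18% | 5–29% |
| Site and epoch effects | independence | 23–26% | 5–11% |
| Site effects, linear time | independence | 15–17% | 4–11% |

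The sandwich standard error was 0.56 to 0.90 of the true SD of the estimate. Further runs of the epoch-effect, exchangeable case widened the limits to 26–39% (sandwich) and 7–19% (model-based).

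With site effects and a model-based standard error, rejection was 4.4–6.2% without site-by-epoch variation and 5.5–10.6% with it; further runs with assumed site-by-epoch variation reached 18%. Independence without site effects is near nominal only at ICC 0.

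A small check of logistic caseness (400 runs per setting, epoch effects, exchangeable, some convergence warnings) gave about 33% with the sandwich and 14–17% model-based.

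**Candidate remedies, same layout, continuous outcome.**

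- t on 4 df with the uncorrected sandwich: 6–25%. Not enough.
- Mancl-DeRouen correction with a normal reference: 6–12%. Not enough.
- Mancl-DeRouen correction with t on 4 df (5 − 1): 2.2–5.9%.
- Cell-mean regression: 30 means less 12 parameters (intercept, 4 site, 6 epoch, 1 Intervention) leaves 18 df. Rejection was about 4–5% under exchangeable site and site-by-epoch variation, and at most 6.2% under a decaying correlation.

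**The case against.** The strongest reply is that the article does not choose the failing implementation. It names GEE and leaves the rest open. A reader who takes the promise to account for sites and times as fixed site and time effects, with a model-based standard error, gets about 4–11%, near nominal if sites are stable over time. A GEE with a bias correction and a t reference holds its level. Such details commonly sit in an analysis plan, and none is shown here.

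Much of this stands, and it rules out several stronger readings that a reader might infer:

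- That the test has a false-positive rate of at least 10%. The document fixes neither the standard error nor the ICC, and some admissible readings are close to 5%.
- That GEE must be abandoned. The fault lies in the variance estimator and reference distribution, which can be corrected.
- That calling the model hierarchical and then implementing GEE is a contradiction with consequences. It can be read as loose wording for patient-level clustered data, and it has no bearing on the error rate.
- That site characteristics cannot be fitted at all. Five sites allow up to four site-level contrasts. Such covariates are redundant only once site effects are in the model.

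What the reply does not remove is that the article itself fixes a large-sample method on 5 clusters. The uncorrected sandwich with a normal reference, the usual GEE inference, rejected at least 15% of the time in every setting tried.

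**Conclusion.** The point holds in conditional form. GEE with 5 site clusters and no stated safeguard is a method the article fixes, and its common implementations do not hold a 5% level in this layout: about 15–39% with the uncorrected sandwich and normal reference, and about 7–19% with an exchangeable model-based standard error. Control near 5% depends on a particular combination, site and time fixed effects with a model-based standard error, and on little site-by-epoch variation, which the article has no data to support.

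The figures rest on an assumed two-sided 5% level, assumed ICCs of 0 to 0.10, full recruitment of 20 per cell and a continuous outcome; evidence for caseness is limited to the small logistic check. That unstated choices can move the error rate from about 5% to over 30% is itself reason to settle them before the data are analysed.

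**What to change.** Add to the Quantitative analysis section one primary inference that is valid with 5 clusters. Either would serve:

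1. Keep the GEE clustered on site; state the working correlation and the site and time terms; use a bias-corrected (for example Mancl-DeRouen) sandwich standard error; refer the statistic to t on 4 df. If site effects are fitted, the correction needs a generalised inverse, and the test was then conservative (2.2–3.0% with site and epoch effects).
2. Form the 30 site-by-epoch means, after any patient-level case-mix adjustment; regress them on fixed site effects, fixed epoch effects and Intervention; use t on 18 df.

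State the significance level. Leave out site-level covariates wherever site effects are fitted. Check the chosen method by simulation for caseness, since both remedies were tested on a continuous outcome only.

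The cost is wording, wider intervals and lower nominal power. The critical value rises from 1.96 to 2.78 (4 df) or 2.10 (18 df). For option 2, the Intervention coefficient has variance 0.657 times the cell-mean variance. At ICC 0 that gives SE = √(0.657 × 81/20) = 1.63, and power for 2.52 points of about 31%. Over the ICC settings simulated it is about 23–32%, before any gain from baseline adjustment. An uncorrected test would not restore that power; it would only hide the shortfall.

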#### Qualitative analysis

Semi-structured interviews with health professionals will be tape-recorded, transcribed verbatim and analysed to determine similarity of themes or differences between barriers to delivery of supportive care previously identified [46]. Clinical Case Review sessions will be recorded, transcribed and similarly analysed.

A random selection of 10% of all HP log books will be examined to determine adherence to the training and identify patterns of referral (for example because of pain) and delineate professional, patient or system barriers to delivery of the Intervention.

## Discussion

This study will examine the effectiveness and feasibility of a model of psychosocial care in which patients are systematically screened for psychosocial needs and risk and then assigned to receive therapy tailored to their precise level of need. Use of novel and readily accessible service providers to deliver the Intervention after participation in focused training is an innovative approach designed to improve patient access to timely psychosocial care, and represents an efficient approach in the face of limited access to scarce psychosocial resources. Inclusion of patients who are considered at risk of anxiety and depression even if not currently distressed is an important strategy to examine the potential to prevent the development of more serious distress. The brief flexible mode of delivery as part of cancer clinicians' routine practice is aimed to address the stigma of psychosocial care and facilitate uptake by patients whose physical condition would make attendance for longer therapies difficult. Incorporation of clinical supervision is a central platform to assist health professionals delivering the Intervention, ensure quality of care, monitor patient responses and reduce the potential for development of health professional stress. The incorporation of in-depth interviews with health professional participants and detailed analysis of the process of clinical supervision will provide fine-grained insights into enablers and barriers of this model of care and guide refinement before its more widespread implementation. Recognition of emotional distress as a vital clinical sign in cancer care has been a major achievement in cancer care policy. One of the barriers to achieving the intended goals of such policy in psychosocial care is the effective translation of the substantial body of evidence regarding screening and psychosocial treatments into routine clinical practice by a range of cancer clinicians in a range of settings. This study aims to help address this gap in knowledge, by training health professionals who work closely with cancer patients in daily practice. More importantly an innovative component of this study is the support and mentoring of health professionals providing psychosocial care as a strategy to bridge knowledge and practice change, while using mixed methodology to study the processes of such clinical practice change.
